### Trial design {8}

This is a single-center, prospective, two-arm randomized controlled trial designed to assess the effects of Argentine tango for people with breast cancer and CRF. The participants will be randomized to either the tango group or the waiting-list control group (Fig. 1). Evaluation of the patient-reported outcomes CRF, sleep quality, and HRQL will be performed.

**Fig. 1 Fig1:**
[figure not shown]
Flow diagram of the study participants according to the Consolidated Standards of Reporting Trials (CONSORT 2010), illustrating the participant’s timeline

## Methods: participants, interventions, and outcomes

### Study setting {9}

This study is conducted by the Forschungsinstitut Havelhöhe (FIH) at the hospital Gemeinschaftskrankenhaus Havelhöhe in Berlin (GKHB). Participants are recruited at the primary care facility of the Breast Cancer Centre at the GKHB.

### Eligibility criteria {10}

#### Inclusion, exclusion, and dropout criteria for participants

Participants will be eligible to join the study if they had been diagnosed with breast cancer, have increased levels of fatigue, are willing to participate in this study, and if they meet all following criteria:
Signed written informed consentAge ≥ 18 yearsStage I–III breast cancer has been diagnosed 12–48 months before enrollmentIncreased levels of fatigue (≥ 12 points in the CFS-D questionnaire)Eastern Cooperative Oncology Group (ECOG) performance status 0–2

Patients will not be eligible for the study if they meet one or more of the following exclusion criteria:
No fatigue at all (≤ 12 points in the CFS-D questionnaire)Pregnancy or breastfeedingOccurrence of recurrences or metastasesConcurrent participation in other clinical trialsLinguistic, medical, psychiatric, cognitive, or other conditions that may compromise the patient’s ability to understand the patient information, comply with the study protocol, or complete the study

Participants must attend at least four of the six tango sessions and answer the questionnaires; if they do not, they will be considered dropouts.

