
### Objectives {7}

This study protocol describes a randomized controlled trial for patients with breast cancer and increased CRF receiving either Argentine tango in a tango group or no Argentine tango in a waiting-list control group. The primary outcome measure is the change of CRF levels after 6 weeks. (A) The CRF changes of patients of the tango group will be compared to the waiting-list control group, and (B) prior to and post the 6-week Argentine tango treatment, the CRF changes are evaluated for the whole study cohort. The primary hypothesis is that a module consisting of six consecutive weekly 1-h Argentine tango lessons will promote a significant reduction of fatigue symptoms. Secondary objectives are the improvement of self-reported sleep quality and HRQL, prior to and post the Argentine tango treatment, and to explore the effects after 6, 12, and 24 months follow-up.

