### Interventions

#### Explanation for the choice of comparators {6b}

The comparator is a waiting-list control group. All participants will be randomized to either the tango group or the waiting group. The participants of the waiting group will continue routine activities during the 6-week waiting period. During follow-up, patients from the waiting-list control group will receive the same Argentine tango module as the participants of the tango group. The follow-up assessments for both trial arms will be the same (Fig. 1).

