### Methods in analysis to handle protocol non-adherence and any statistical methods to handle missing data {20c}

Patients who are unable to participate in the tango treatment or withdraw consent to participate in the study will be excluded and not replaced. If individual sessions cannot be attended, this will be noted, and the surveys will continue as planned. Regarding the evaluation of the questionnaires, we follow the EORTC-QLQ-C30 scoring manual on the calculation and handling of missing data. We do not plan to use imputation when reporting outcome data.

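### The rules on attendance and taking part in tango define the analysis set by behaviour after randomisation, and at week 6 only the tango arm can fail them; no as-randomised analysis is stated

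*Protocol article*

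**What the plan says.** Four parts of the protocol article bear on who enters the primary comparison.

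- **Eligibility criteria {10}:** "Participants must attend at least four of the six tango sessions and answer the questionnaires; if they do not, they will be considered dropouts".
- **Section {20c}, on non-adherence and missing outcomes:** "Patients who are unable to participate in the tango treatment or withdraw consent to participate in the study will be excluded and not replaced". The next sentence reads "If individual sessions cannot be attended, this will be noted, and the surveys will continue as planned", and the section ends "We do not plan to use imputation when reporting outcome data".
- **Sample size {14}:** 25 per group are needed. A 20% dropout rate is added to reach 60 randomised, so dropouts are budgeted as contributing nothing.
- **Objectives {7}:** "The primary outcome measure is the change of CRF levels after 6 weeks". For comparison (A), "The CRF changes of patients of the tango group will be compared to the waiting-list control group".

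The control arm's exposure is set out under the choice of comparators {6b}: "The participants of the waiting group will continue routine activities during the 6-week waiting period". Tango comes later for them: "During follow-up, patients from the waiting-list control group will receive the same Argentine tango module as the participants of the tango group".

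No section says that participants are analysed in the arm to which they were randomised, whatever their attendance.

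**The concern.** Randomisation makes the two arms comparable at baseline, and that holds only while the analysed groups are the randomised groups. Here membership of the analysed group depends on what happens afterwards: sessions attended, being able to take part in tango, questionnaires returned, consent maintained.

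Two of these criteria are asymmetric at the primary time point. Up to week 6 the waiting list has no sessions to miss and no tango treatment to be unable to join, so only tango participants can fail. If the rule were applied to controls once they take their own module, and then carried back to comparison (A), it would remove them for behaviour after their primary endpoint.

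Attendance is plausibly related to the outcome. The Background {6a} names fatigue and poor motivation, along with lack of time, as barriers to physical activity. If those whose fatigue is not improving stop coming, deleting them from one arm creates an apparent benefit.

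The t-test named in Statistical methods {20a} does nothing about this. The adjusted regressions in {20a} and {20b} can account for measured baseline differences among those retained, but not for selection on how fatigue changed after randomisation.

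**Working it through.** **1. The plan's own figure.** Inputs from Sample size {14}: d = 0.8, power 80%, two-sided 5%.

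n per group = 2 × (1.960 + 0.842)² / 0.8² = 24.5, rounded up to 25. This reproduces the stated number (the exact t-test gives 25.5, so 26). The total of 60 is 50 × 1.20. Whether that is the right inflation is a separate matter. What counts here is that the calculation leaves dropouts out of the analysed number.

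**2. Which arm can fail which criterion before week 6**

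| Criterion | Tango | Waiting list |
|---|---|---|
| Fewer than 4 of 6 sessions ({10}) | yes | no |
| Unable to take part in tango ({20c}) | yes | no |
| Questionnaires not answered ({10}) | yes | yes |
| Consent withdrawn ({20c}) | yes | yes |

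**3. Size if those doing worse leave.** Assumptions: no true effect; 30 per arm; 6 of 30 (20%) removed from tango and none from the waiting list; removal driven by a latent variable with correlation c to a worse change.

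Large-sample bias = c × φ(z₀.₂₀) / (1 − 0.20) = c × 0.280 / 0.80 = 0.35c SD. Simulation with exactly 6 of 30 removed and a two-sample t-test gives:

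| c | Spurious benefit (SD of change) | Two-sided type I error |
|---|---|---|
| 0 | 0 | 5% |
| 0.3 | 0.10 | about 7% |
| 0.5 | 0.17 | 10% |
| 0.7 | 0.24 | 15% |
| 1.0 (extreme bound) | 0.34 | 28% |

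At c = 0.5, the same selection in both arms gives no bias and a type I error of about 6%. The asymmetry does the damage.

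**4. Selection in the other direction.** Suppose instead that the 20% with the highest baseline fatigue leave the tango arm. Take equal SDs before and after, and an assumed pre-post correlation r. Those retained start lower by about 0.35 SD, and regression to the mean shifts their change upwards.

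Bias against tango, in SDs of the change = 0.35 × (1 − r) / √(2(1 − r)). This is 0.17 for r = 0.5 and 0.14 for r = 0.7; with exactly 6 of 30 removed, 0.17 and 0.13.

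**5. Power (two-sample t-test)**

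| Analysed | d | Power |
|---|---|---|
| 24 v 30 (20% removed from tango only) | 0.80 | 82% |
| 30 v 30, all scores obtained, no dilution | 0.80 | 86% |
| 30 v 30, 20% non-adherers gain nothing: 0.8 × 0.8 | 0.64 | 68% |

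**The case against.** The strongest objection concerns the text. Eligibility {10} calls low attenders dropouts; it does not say that their data leave the analysis. The explicit exclusion in {20c} covers only those unable to take part in tango and those withdrawing consent. For missed sessions the same section keeps the surveys going, which can be read as retaining partial attenders. A reader might infer that their week-6 scores are collected and then thrown away. No section says so. What stands is that removal of those attending one to three sessions is a strong inference from {10}, {14} and {20c} together, and that {10} and {20c} have to be reconciled.

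Second, a reader might call the whole exclusion one-sided. Only attendance and tango participation are; non-response and withdrawal can occur in both arms.

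Third, a reader might conclude that the bias must favour tango. The documents do not establish this. Lack of time is also listed as a barrier and need not relate to outcome, and the endpoint is change rather than level. Step 4 shows a plausible selection that works against tango.

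Fourth, the 20% is the plan's overall dropout allowance, not an attendance-failure rate for one arm, and the protocol describes phone contact to keep people attending ({11b}, {11c}, {18b}). The simulated figures are therefore illustrations under assumptions, and c = 1.0 is a bound.

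Fifth, keeping everyone need not raise power: if non-adherers gain nothing it falls from 82% to 68%.

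None of this supplies an as-randomised analysis, and none of it removes the explicit exclusion of those unable to take part.

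**Conclusion.** The point holds and should be settled before the primary analysis. As written, the plan conditions the 6-week randomised contrast on behaviour after randomisation, through two criteria that only the tango arm can fail by then. The exclusion is explicit for those unable to take part in tango and a strong inference for those attending one to three sessions.

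The size cannot be computed from the documents. If 20% are lost from the tango arm alone and those doing worse tend to leave, the contrast is shifted towards tango by about 0.10 to 0.17 SD at correlations of 0.3 to 0.5, with type I error of about 7 to 10%; the bound is 0.34 SD and 28%. Selection on high baseline fatigue could shift it by 0.13 to 0.17 SD against tango, for an assumed pre-post correlation of 0.7 to 0.5. The direction is therefore open. Exposure to bias is what the text supports.

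**What to change.** - State that comparison (A) analyses every randomised participant in the allocated arm, regardless of sessions attended.
- Seek the week-6 CFS-D from everyone who has not refused further data collection, including those who stopped or never started tango.
- Use all available week-6 scores, and add a sensitivity analysis for missing ones, for example with worse values assumed for non-responders.
- Keep attendance of at least four of six sessions as the definition of a secondary per-protocol set.
- In {20c}, limit the exclusion to data collection after consent is withdrawn, so that it no longer covers patients unable to take part in tango. Reconcile it with the dropout definition in {10}.

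The cost is wording, some effort to obtain week-6 questionnaires from non-attenders, and a little more analysis. Session counts are already to be recorded ({11c}), and the trial was still enrolling at the stated status. The estimate may be diluted, and power could be 86% or as low as about 68% depending on what non-adherers gain, against 82% for 24 v 30. The change is justified by a valid comparison, not by a gain in power.

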### Who will take informed consent? {26a}

It is the responsibility of the study physician to provide sufficient verbal and written information on the study’s purpose and procedures, information on data protection procedures, possible advantages and disadvantages of participation, and option to withdraw from the study at any time and without any given reason and to take informed consent. Written informed consent will be obtained from all participants prior to study enrollment.

### Additional consent provisions for collection and use of participant data and biological specimens {26b}

The consent form asks whether participants agree that the data collected may be shared and published in a pseudonymized form for research purposes.

### Interventions

#### Explanation for the choice of comparators {6b}

The comparator is a waiting-list control group. All participants will be randomized to either the tango group or the waiting group. The participants of the waiting group will continue routine activities during the 6-week waiting period. During follow-up, patients from the waiting-list control group will receive the same Argentine tango module as the participants of the tango group. The follow-up assessments for both trial arms will be the same (Fig. 1).

#### Intervention description {11a}

The Argentine tango program consists of six weekly 1-h tango sessions, which are conducted by a professional tango teacher and will be carried out in small groups of three to eight participants. Elements of movement and music of Argentine tango will be presented. The coordination, rhythm, and body awareness will be stimulated with harmonic movements to the tango music. Introductory exercises are practiced first without musical accompaniment and then with Argentine tango music. The 6-week program comprises breathing and relaxation exercises, balance finding, and includes tango walking and dancing elements as well as social interaction. The therapist will give explanations and lead guided exercises which are oriented towards walking to music, self-perceptions, and spatial perceptions as outlined in Table 1. Each group session will be structured in a warm-up, main part, and focused ending. The warm-up consists of a standing exercise with the feet open, with the imagination of moving through the body from the toes to the scalp and bringing awareness to the bodily sensations. The main parts have different focuses throughout the six sessions and include theoretical and practical instructions of walking and dancing techniques, repetitions with individual breaks, and explanations as needed (for details see Table 1). Each session ends with a 3-min standing exercise without movement, in silence with feet open and eyes closed.

**Table 1 Tab1:** Six-week Argentine tango protocol for people with breast cancer and fatigue

Session	Description of the activities
1	***Self-awareness*****.** Warming-up (standing exercise, open feet, imaging of moving through the body from toes to scalp bringing awareness to patient’s bodily sensations); axis and muscle tone; tension and relaxation; introduction of the tango position with feet closed, reaching in six directions (floor, sky, front, back, left, right); walking techniques, steps in four directions (forward, backward, left, right); walking forward in the line of dance with music; walking backward in the line of dance with music; changing directions in the line of dance from forward to backward while walking with music; and focused ending (standing exercise in silence with open feet and eyes closed, no movement)
2	***Spatial and musical perception*****.** Warming-up; walking technique, steps in four directions; walking in the line of dance to the music; changing directions in the line of dance from forward to backward while walking with music; musicality: double-beat, single-beat, and half-beat; focused ending
3	***Social Perception.*** Warming-up; walking technique, steps in four directions; walking in the line of dance to the music; changing directions in the line of dance from forward to backward while walking with music; musicality: double-beat, single-beat, and half-beat; partner exercises “mirror dance” = no physical contact, distance 2 m; mirror dance in a circle: one person leads the whole group; mirror dance in couples with changing partners walking in squares and walking in the line of dance with music; and focused ending
4	***Playfulness*****.** Warming-up; introduction of the “pivot” = turning on one foot; combining walking and pivot; mirror dance (distance 2 m, no physical contact) in couples with changing partners with playful variations of walking together in the line of dance with music and with pivots; and focused ending
5	***Sensation*****.** Warming-up; mirror dance in couples (distance 2 m, no physical contact) with changing partners with the elements of the previous four sessions; focus on the quality of movement and connection = not how we move matters, but how we feel moving; and focused ending
6	***Shared experience*****.** Warming-up; dancing summary of the five sessions; focus on communal dance experience (distance 2 m, no physical contact); combining oneself with the group; and focused ending

#### Criteria for discontinuing or modifying allocated interventions {11b}

Participants are encouraged to report any discomfort and to perform only movements that do not cause them any problems. If a participant does not attend a session, she is contacted by phone and asked how she is feeling, and options are sought to continue her tango sessions. Adapting to the current COVID-19 pandemic conditions, the tango sessions are conducted in compliance with the national security and hygienic regulations, i.e., all dance movements, including paired actions, will be performed at a distance of 2 m to each other, the tango sessions will be conducted in a large therapy room with adequate oxygen ventilation, and the patients as well as the teacher are wearing surgical masks during the session. Before entering the therapy room, the teacher and the patients have to disinfect their hands with adequate disinfection detergent (including > 75% ethanol). Protective policies are constantly adapted to the locally applicable regulations; currently, participants must be vaccinated or have a valid negative SARS-CoV2 test to participate in Tango sessions.

#### Strategies to improve adherence to interventions {11c}

At the beginning of each session, participants are asked about their feelings with the previous session and experiences, and their preferences are discussed in the group. In case of any problems with adhering to the tango lesson, ways will be sought to carry out at least minimal essential parts of the treatment. The number of sessions each participant actually attended will be recorded. For the follow-up surveys, questionnaires will be sent with prepaid return envelopes, and if necessary, participants will be reminded by phone call to fill in and return them.

#### Relevant concomitant care permitted or prohibited during the trial {11d}

Concomitant medications including nutritional supplements, vitamins, and natural remedies will be registered in the case report form. Standard routine care and drugs as endocrine treatments do not affect patients’ eligibility to enter or patients’ participation during the trial.

#### Provisions for post-trial care {30}

After the whole tango module, participants will be provided with information about appropriate online tango exercises and classes that they could attend on a self-pay basis.

### Outcomes {12}

Outcome measures are 1. the change of CRF levels, 2. the change of sleep quality, and 3. the change of HRQL.
CRF levels will be investigated with the German version of the certified and validated Cancer Fatigue Scale (CFS-D) [30]. It consists of a 15-item questionnaire on three subscales (physical, cognitive, and affective fatigue), based on a 5-point Likert scale with a possible range of 0 (no fatigue) to 60 (maximum fatigue) [30]. The CFS-D is highly reliable with a robust validity and classifies values ≥ 30 points as clear symptoms of fatigue, ≥ 24 points as suspected moderate fatigue, and ≤ 23 points as only minor or no fatigue symptoms. A decline of scores indicates an improvement of fatigue while higher scores represent a higher degree of fatigue symptoms.Self-reported sleep quality will be evaluated by the certified and validated Pittsburgh Sleep Quality Index (PSQI) questionnaire [31]. This questionnaire is composed of seven sleep-related subscales (subjective quality, latency, duration, habitual efficiency, disturbances, use of sleeping medication, and daytime sleepiness) all scored between 0 and 3. The global PSQI sum scores range from 0 (no sleep disturbance) to 21 (maximally disturbed sleep), while a PSQI score greater than 5 classifies poor sleepers.Self-reported HRQL will be investigated with the European Organization for Research and Treatment of Cancer Questionnaire C30 (EORTC-QLQ-C30) [32], which is structured into 15 different subscales (1 global health, 5 functional, and 9 symptoms, including fatigue and insomnia scales). Equations will be made as described in the EORTC-QLQ-C30 manual. The EORTC scores range from 0 to 100, and higher scores represent a better self-reported level in the functional dimensions but a higher degree of symptom burden.

*Baseline information* on diagnosis, such as histology, tumor classification, and potential previous treatments, will be collected from the clinical interview at study inclusion and the participants’ medical records. All participants will be asked to answer all questionnaires at baseline, prior to and post-treatment, or waiting, and likewise in the framework of mid- and long-term surveys, 6, 12, and 24 months after completing the tango module (Fig. 1). Follow-up surveys will also ask about interim experiences with dance and movements, what medications were taken, and whether there are interests in continuing and online interventions. The courses of fatigue, sleep quality, and HRQL of participants of this study will be compared to those of previous patients of the GKHB Breast Cancer Center [18, 33].

### Participant timeline {13}

In Fig. 1, trial procedures from enrollment to the end of the trial are illustrated.

### Sample size {14}

The expected longitudinal differences between the means of the outcomes assessed will be estimated based on our previously published breast cancer studies [18, 33]. Previously, significant associations with medium effect sizes between non-pharmacological interventions and an improvement in fatigue were observed, and we found a mean difference of 7–12% [33]. For the characterization of the group and longitudinal differences, Student’s *t*-tests and Pearson’s chi-squared tests with Yates’ continuity correction were performed. For the calculation of the sample size, medium to large effect size differences (Cohen’s *d* of 0.8) and a power of 80%, as well as a significant level of 5% (two-sided) for the primary outcome fatigue, are assumed. Thus, a case number of 25 patients per group will be necessary. Assuming a dropout rate of 20%, we need to recruit and randomize 60 participants.

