### Assignment of interventions: allocation

#### Sequence generation {16a}

The randomization sequence has been created [34] using the website www.jerrydallal.com/random/random_block_size_r.htm with a 1:1 allocation, using block sizes of four to six. The randomization plan for subjects no. 1–40 was generated on 12 May 2020 (Seed No. 15277) and for subjects no. 41–60 on 2 March 2021 (Seed No. 15434).

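### Sixty randomised with 20% dropout leaves 24 per group, not the stated 25, and about 77% power at d = 0.8 by the planned t-test; d = 0.8 should be labelled large

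*Protocol article*

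**What the plan says.** Everything in the calculation stands in the protocol article under Sample size {14}. The effect is described as "medium to large effect size differences" and set at a Cohen's d of 0.8. Power is 80%, with "a significant level of 5% (two-sided) for the primary outcome fatigue". The result is that "a case number of 25 patients per group will be necessary". The allowance for losses follows: "Assuming a dropout rate of 20%, we need to recruit and randomize 60 participants". Allocation is equal (Sequence generation {16a}: "with a 1:1 allocation, using block sizes of four to six").

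The same section supports the effect size with the group's earlier work, in which "significant associations with medium effect sizes between non-pharmacological interventions and an improvement in fatigue were observed". It adds a mean difference of 7–12% but gives no d and no SD.

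Three other sections decide how dropout reaches the analysis. Eligibility criteria {10} counts as a dropout anyone who attends fewer than four of the six sessions or does not answer the questionnaires. Section {20c} excludes, without replacement, patients who cannot take part or who withdraw consent, and it plans no imputation. Section {20a} names Student's t-test, with p below 0.05 as the criterion.

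**The concern.** If 25 per group are needed and a fifth of patients will be lost, the number randomised must still leave 50 after the loss. Sixty does not. The section therefore promises a size and a power that its own assumptions do not deliver, and a reader would repeat 80% as the design power.

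The label matters for a related reason. On Cohen's scale for d, 0.5 is medium and 0.8 is large. Calling 0.8 medium to large suggests that the trial has adequate power for effects well below 0.8, and the calculation does not show that. When a non-significant result is interpreted, the reader should know which effect the trial was built to detect.

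**Working it through.** **Inputs.** From Sample size {14}: d = 0.8, power 80%, two-sided alpha 5%, dropout 20%, 60 randomised. From Sequence generation {16a}: 1:1 allocation. From {20a}: Student's t-test.

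**Step 1: reproduce the 25.** Normal approximation: n per group = 2(1.960 + 0.842)²/0.8² = 2 × 7.849/0.64 = 24.5, so 25. The plan's figure reproduces. The exact calculation for the t-test (noncentral t) gives 25.5, so 26. A one-sided test would give 20, so the two-sided reading is the one that fits.

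**Step 2: the dropout allowance.**
- As stated: 50 × 1.2 = 60.
- What 60 leaves: 60 × 0.8 = 48, or 24 per group.
- What 50 evaluable requires: 50/0.8 = 62.5, so 63, or 64 for equal arms.
- Largest dropout at which 60 still leaves 50: 1 − 50/60 = 16.7%.

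**Step 3: power at d = 0.8.** For n per group, the noncentrality is 0.8 × √(n/2) with 2n − 2 degrees of freedom. At n = 24 it is 0.8 × √12 = 2.77, with 46 degrees of freedom and critical value 2.013.

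| n per group | t-test (exact) | normal approximation |
|---|---|---|
| 24 | 77.4% | 79.1% |
| 25 | 79.1% | 80.7% |
| 26 | 80.7% | 82.2% |

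The effect detectable with 80% power at 24 per group by t-test is d = 0.83. If the same 48 were split unevenly, power would be slightly lower: 77.1% at 22 and 26, and 76.3% at 20 and 28.

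**Step 4: smaller effects (assumed values, not figures from the protocol).** T-test power at 24 per group is 39.6% at d = 0.5, 53.0% at d = 0.6 and 66.1% at d = 0.7. With all 60 analysed (30 per group), d = 0.5 gives 47.8%.

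**Step 5: does the earlier medium effect contradict d = 0.8?** Section {20a} grades effects by R², with 13–25% as medium. If such an R² came from a two-group comparison alone, d = 2√R²/√(1 − R²):
- R² = 13%: 2 × 0.361/0.933 = 0.77.
- R² = 25%: 2 × 0.5/0.866 = 1.15.

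On that reading, a medium effect is compatible with d = 0.8. On the d scale, it would be about 0.5. The document does not say which scale applies.

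**The case against.** The strongest reply is that the slip is trivial. It costs one patient per group. By the formula that reproduces the plan's 25, power is still 79.1%, and 20% dropout is itself only a guess. The 25 is a standard normal-approximation result, so needing 26 by the exact test is no defect. An analysis adjusted for the baseline score could restore the power: section {20b} lists baseline outcome values among the covariates, and with an assumed baseline correlation of 0.3, power at 24 per group is about 81%. All of this is fair and sets the severity. It does not make 60 × 0.8 equal 50. The stated power is also tied to no adjusted analysis: the method named in the section is the t-test, and the adjusted models in {20a} and {20b} are described as ways to address confounders and influencing factors.

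A reader might go further and infer that the calculation rests on an effect larger than its own source, so that the trial has only about 40% power for what the earlier studies found. The document does not support that. The earlier medium effect comes without a d or an SD and concerns associations. It may have been graded by R², where medium can correspond to a d near 0.8 (Step 5). The 40% belongs to an assumed d of 0.5.

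Nor does the wording mislead as badly as it could: d = 0.8 is printed beside the label, and {20a} promises effect size estimates alongside significance tests. The label is still loose and easily corrected.

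**Conclusion.** The point holds as a minor error. Under the plan's own 20% dropout, 60 randomised gives 48 evaluable, or 24 per group, and not the 25 called necessary. Power at d = 0.8 is 77.4% by the planned t-test: 2.6 points below the stated 80%, or about one point below by normal approximation. To keep 25 per group, 63 would have to be randomised (64 for equal arms).

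This assumes equal loss in the two arms, dropouts absent from the analysis as {10} and {20c} imply, and an unadjusted comparison. The figure of 25 is acceptable as an approximation and is not an error in itself. The label for d = 0.8 should be large. Whether 0.8 exceeds the earlier evidence cannot be settled from this document.

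**What to change.** Keep 60 and restate the result in Sample size {14}: *60 randomised with 20% dropout gives 48 evaluable patients (24 per group), which provides about 77% power by unadjusted two-sided t-test for a large effect (d = 0.8) and 80% power for d = 0.83.* Replace the medium-to-large label with large.

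If power for smaller effects is added, mark it as an assumption: about 40% at d = 0.5, 53% at 0.6 and 66% at 0.7. If a baseline-adjusted analysis is made primary, recompute the power on that basis and state the assumed correlation.

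The cost is a few sentences and a slightly less favourable power figure. No extra patients are needed. According to Trial status, recruitment was still open, so the change can be made before results are known.
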